### Outcome measures

#### Primary outcomes

##### Efficacy

The primary outcome is the home-based overnight supine BP recorded four times with the 24-hour ambulatory blood pressure measurement (ABPM). This recording will be done during one of the last three days of every phase. The measurements during the baseline horizontal week will be used to calculate the change score to determine the effect of each angle on the BP. The BP device will measure the BP every half hour during the night, according to the guidelines for ABPM measurements [29]. Participants will self-report the actual time they spend lying down in bed.

**Table 1 Tab1:** Overview of study procedures

Activity	In-clinic 1	Wk1	Wk2-3	Wk4-5	Wk6-7	In-clinic 2
Informed consent	X					
Demographics	X					
Tilt-table and BP standing test	X					X
MDS-UPDRS	X					X
Questionnaires OHQ, PSQI, FES, selected questions from SCOPA, PDQ-39, HADS and MHC-SF	X					X
Timed Up and Go test	X					X
Average overnight and daytime BP with 24-h ABPM (4x)		X	X	X	X	
Supine BP (daily, 45x)		X	X	X	X	
Standing BP (guided, 4x)		X	X	X	X	
Questionnaire on phone app (4x) - OHQ - ICIQ-N - Number of falls - Nocturia - Subjective comfort of HUTS		X	X	X	X	
Nocturia measurements - Body weight (45x) - Nighttime urine production (4x)		X	X	X	X	
Interview on barriers and facilitators of HUTS						X

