##### Tolerability

We will evaluate the tolerability of HUTS with four indicators: (1) compliance, as measured by the daily question if they slept in the right angle, presented as proportion of participants that were > 80% of the study period compliant to the prescribed intervention; (2) the proportion of participants who did not tolerate the angle and returned to the previous angle; (3) the number of dropouts and if provided their reason for dropping out of the study, and; (4) reported barriers and motivators for using HUTS (evaluation during the final in-clinic session).

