#### Final analysis

After completion of the study the data will be analyzed according to the intention-to-treat principles. For the main analysis of the overnight BP measured with the 24-hour ABPM in each phase we will use the overnight BP measured in week 1 as baseline to determine the change score. The 1° angle will serve as placebo, and the rest of the HUTS angles are grouped together for overall effectiveness and the increasing angles separately for determining which angle is the most effective for reducing the overnight BP. To estimate the effect of the HUTS angle we will use a linear mixed model with as a dependent variable the change in overnight BP as measured during the 24-hour ABPM, with fixed effects for angle, group and visit and with a random effect for subject. As covariables the baseline BP value, age and disease duration will be used. The within group differences will also be analyzed for all angles with a linear mixed effects model per group. Dependent variables in this calculation are the angle (fixed effect) and subject (random effect). The daytime variation will be calculated in the same way as described for the overnight BP.

The secondary outcome morning supine BP will be analyzed by averaging the three consecutive morning measurements and comparing the 13 timepoints from each phase with the baseline for overall effect, and by comparing each of the three phases to investigate the difference in effect for angles taking into account the time-effect.

Additional explorative analyses based on the per-protocol principles will be performed, this includes the analysis on tolerability of HUTS, baseline characteristics collected at the in-clinic sessions, the results from the PSQI, falls, FES, PDQ-30, HADS and MHC-SF which all will be exploratively analyzed. The tilt table test will be analyzed to investigate the differences between responders and non-responders by looking at the severity of supine hypertension and orthostatic hypotension.

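### The only tolerability analysis described is explorative and per-protocol, although three of its four indicators are themselves departures from adherence or completion

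*Protocol article*

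**What the plan says.** In the protocol article, Outcome measures opens with the heading "Primary outcomes", under which Efficacy and Tolerability are the two subheadings; Secondary outcomes follow. The Efficacy text names one primary outcome: "The primary outcome is the home-based overnight supine BP recorded four times with the 24-hour ambulatory blood pressure measurement (ABPM").

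The Tolerability subsection gives four indicators:

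- Compliance comes first. It rests on a daily self-report of the sleeping angle and is to be "presented as proportion of participants that were > 80% of the study period compliant to the prescribed intervention".
- Step-back is the second indicator, defined in the article as "the proportion of participants who did not tolerate the angle and returned to the previous angle".
- Attrition from the trial is the third, and here the article asks for a count and not a proportion: "the number of dropouts and if provided their reason for dropping out of the study".
- What hindered or helped participants is the fourth and is gathered at the last clinic visit.

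The Final analysis section begins: "After completion of the study the data will be analyzed according to the intention-to-treat principles". After the blood pressure models it states: "Additional explorative analyses based on the per-protocol principles will be performed, this includes the analysis on tolerability of HUTS". The same sentence goes on to list baseline characteristics, PSQI, falls, FES and other questionnaires.

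The Discussion gives the reason for a per-protocol analysis. Participants who do not tolerate a new angle are asked to go back to the previous one, so intention-to-treat is likely to affect the efficacy results at the higher angles. Tolerability is not mentioned in that reasoning.

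**The concern.** A per-protocol set, in the usual sense, is chosen by adherence and completion. Indicators 1 to 3 measure adherence and completion. Choosing the population by the outcome pushes compliance towards 100% and step-back and dropout towards zero, whatever happens in the trial.

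This matters because tolerability is half of the trial's stated aim. The abstract's hypothesis is that higher angles work better but are tolerated less well, and the Discussion says that the results will help decide which angles a phase III trial should study. The bias makes an angle look more tolerable than it is, and it grows with the proportion who fail to tolerate it. It would therefore be expected to be largest at 18°, which only the treatment group uses.

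Falls, PSQI and FES bear on harm, and the same sentence puts them on the same footing. Participants who sleep badly or fall may be among those who abandon the angle, and their data are the ones a set selected on adherence would lose.

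**Working it through.** The article states no tolerability figure and no formal sample size calculation, so there is nothing to reproduce. The check compares the outcome definitions with the analysis set, and then illustrates the size.

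**Indicators against the set**

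| Indicator (Tolerability subsection) | What counts against tolerability | Effect of a set selected on adherence or completion |
|---|---|---|
| Compliance on more than 80% of the study period | Not sleeping at the prescribed angle | Non-compliers leave the set; result moves towards 100% |
| Return to the previous angle | Leaving the scheduled angle | Depends on whether an instructed step-back counts as adherent |
| Dropout | Not completing | Dropouts leave the set; result moves to zero |
| Barriers and motivators | Reported at the last clinic visit | Not a departure in itself, but the interview is tied to completion |

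**Inputs for the illustration**

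- Total sample: 50 (Sample size calculation section).
- Treatment group, the only one assigned to 18°: n = 25. This is an assumption, because the allocation ratio is not stated.
- Participants who do not tolerate 18°: x = 8 of 25. This is an assumption.
- Split of the 8: 4 step back, and 4 drop out or are non-compliant. This is an assumption.

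**Formulas.** With all randomised participants the proportion is x/n. If e of the x are excluded from the set, it becomes (x − e)/(n − e). Intervals are exact (Clopper-Pearson) 95%; for 0/m the upper limit is 1 − 0.025^(1/m).

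**Results for x = 8, n = 25**

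| Population | Calculation | Non-tolerance | 95% CI |
|---|---|---|---|
| All randomised | 8/25 | 32% | 14.9% to 53.5% |
| Dropouts and non-compliers excluded (e = 4) | (8 − 4)/(25 − 4) = 4/21 | 19% | 5.4% to 41.9% |
| Step-backs excluded too (e = 8) | (8 − 8)/(25 − 8) = 0/17 | 0% | 0% to 19.5% |

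**Range over the assumed rate, all non-tolerators excluded**

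| All randomised | 95% CI | Per-protocol | Upper 95% limit |
|---|---|---|---|
| 2/25 = 8% | 1.0% to 26.0% | 0/23 | 14.8% |
| 5/25 = 20% | 6.8% to 40.7% | 0/20 | 16.8% |
| 8/25 = 32% | 14.9% to 53.5% | 0/17 | 19.5% |
| 10/25 = 40% | 21.1% to 61.3% | 0/15 | 21.8% |

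The zeros in the second table follow from the assumption that every non-tolerator is excluded. They show the limit of the problem and do not predict what this trial would report. For any e > 0 with x < n, (x − e)/(n − e) is smaller than x/n, so the direction does not depend on the assumed values.

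**The case against.** **The set is undefined, and stepping back is an instructed step.** This stands. A participant who goes back to the previous angle when asked may well be counted as following the protocol. A reader might infer that the plan removes everyone who did not tolerate an angle and will report 0%; the article does not say so. Zero is the extreme case. A set that keeps the step-backs still loses dropouts and non-compliers, so the direction remains.

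**The sentence may be loose drafting.** The section opens with intention-to-treat, the later analyses are called additional, and the list includes baseline characteristics. The indicators are worded as proportions of participants and a count of dropouts, and a set without dropouts cannot count them. This makes it plausible that the authors intend to use all participants. But no such analysis of tolerability is described, and an analysis plan that follows the sentence would inherit the problem.

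**Dropouts are not silent.** This also stands. A reader might infer from the final-visit interview that those who leave are never heard. In fact, reasons for dropout are recorded if provided, comfort is rated in each phase (Table 1), and four video calls are planned. Only the formal interview is tied to the last visit.

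**Harm is also captured elsewhere.** Adverse events are to be registered by treatment phase and group, and nothing places them on per-protocol principles. The concern about harm is confined to falls, PSQI and FES.

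**Tolerability is primary by heading only.** This is correct: the abstract and the Efficacy text both name overnight blood pressure alone. Tolerability standing under a primary heading and then being called explorative is a labelling inconsistency. It does not show that a primary endpoint was demoted, and the population problem does not depend on it.

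**Conclusion.** The concern holds. As written, the article assigns tolerability, falls, PSQI and FES to explorative per-protocol principles and describes no intention-to-treat analysis of tolerability. Its own reason for a per-protocol analysis reaches only the efficacy of the higher angles. Followed literally, the plan biases tolerability in the favourable direction.

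The size cannot be fixed from the article. With 8 of 25 not tolerating 18°, the reported figure would lie between 4/21 (19%) and 0/17 (0%) instead of 32%. This rests on an assumed rate, an assumed 25 per group, and an assumed equal split between step-backs and dropouts or non-compliers. The primary blood pressure analysis is not affected. The daily compliance answers, step-backs and dropouts are already to be recorded for all participants, so the problem can be fully corrected before analysis.

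**What to change.** - Name all randomised participants as the population for the tolerability indicators, falls, PSQI and FES.
- Report compliance, step-back and dropout (with reasons) separately for each angle. Use all participants assigned to that angle as the denominator and, alongside, all who started it. The second denominator keeps people who left before reaching an angle from being read as evidence about it.
- As a sensitivity analysis only, count dropouts at or after the start of an angle as not tolerating it. Making this the main rule would merge indicators that the article keeps apart and would count departures for unrelated reasons as intolerance.
- Report PSQI and FES by group. Table 1 schedules them only at the two clinic visits, so they cannot be attributed to single angles.
- Keep per-protocol as a supportive analysis of the blood pressure effect, which is the purpose the Discussion gives for it.

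The cost is wording only: no added visits, measurements or participants. Reported tolerability may become less favourable.

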##### Secondary outcomes

The first secondary outcome is the daily supine morning BP. This is measured and reported by the participants themselves before taking a seated position in bed.

During the four video sessions data is gathered on orthostatic BP through supervised home-based standing tests and daytime BP measured by the 24-h ABPM, which records daytime BP three times per hour. Other ABPM parameters will be considered as well (e.g., BP variability and nocturnal dipping).

Besides BP, the symptoms of orthostatic intolerance are determined with the Orthostatic Hypotension Questionnaire (OHQ) [30] and the cardiovascular questions of the Scales for Outcomes in Parkinson’s disease – Autonomic symptoms (SCOPA-AUT) [31]. Nocturia will be quantified during the ABPM measurement by collecting and reporting the total volume of urine produced during the night. On all other days, the overnight weight loss will be used to estimate the total volume lost. The International Consultation on Incontinence Questionnaire Nocturia Module (ICIQ-N) is used to determine the amount of bother experienced as a result of nocturia [32].

At both in-clinic sessions participants will be subjected to a phased tilt table test protocol including heart rate and beat-to-beat BP recordings (Finapres Medical Systems, Enschede, The Netherlands). We will tilt from a horizontal position to 15°, 30°, 45° and finally 60°. This will provide us with systematic measures of BP responses to different degrees of orthostatic positions. This, together with the standing test, will be used to investigate whether clinically relevant predictive values for the effectiveness of HUTS can be identified. Adverse events will be registered and grouped per treatment phase and group.

We selected several questionnaires which will be used to monitor the wellbeing of the participants in multiple areas:

The Pittsburgh Sleep Quality Index (PSQI) [33] to investigate sleep quality, duration and parasomnias, the number of falls during participation, and the fear of falling as determined by the Falls Efficacy Scale (FES) [34].The Parkinson’s Disease Questionnaire (PDQ-39) to evaluate mobility, activities, emotional wellbeing, stigma, social implications, cognitive impairment and bodily discomfort [35].The Hospital Anxiety and Depression Scale (HADS) [36] and the Mental Health Continuum-Short Form (MHC-SF) [37] to monitor the emotional wellbeing of the participants.

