Taken together, HUTS is an attractive intervention with the unique potential to positively impact supine hypertension and orthostatic hypotension simultaneously. Although the intervention seems simple and straightforward, the best way to implement in often frail people with movement disorders needs further study. If the current trial proves successful, a definitive phase III RCT will be designed, powered to study clinically relevant outcomes. The current study will help to determine which angles and target population this new trial should focus on. The current work will lay the foundation for practical guidelines for a structured and personalized application of HUTS.

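### Splitting participants into responders and non-responders to find predictors of HUTS effect discards information that a continuous analysis of the same data would keep

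*Protocol article*

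**What the plan says.** The last paragraph of Final analysis opens with "Additional explorative analyses based on the per-protocol principles will be performed" and closes with the predictor analysis: "The tilt table test will be analyzed to investigate the differences between responders and non-responders by looking at the severity of supine hypertension" and of orthostatic hypotension. Secondary outcomes gives the purpose: the tilt test, together with the standing test, "will be used to investigate whether clinically relevant predictive values for the effectiveness of HUTS can be identified". The tilt test is done twice: "At both in-clinic sessions participants will be subjected to a phased tilt table test protocol". The Discussion adds: "The current study will help to determine which angles and target population this new trial should focus on".

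The article does not say which outcome, angle or cut-off makes a participant a responder. The efficacy change score that it does describe is the overnight ambulatory one. Under Efficacy, "This recording will be done during one of the last three days of every phase", and under Final analysis, "we will use the overnight BP measured in week 1 as baseline to determine the change score". Each such change is therefore one recording minus another.

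**The concern.** The comparison groups people by outcome and then looks back at their severity. Two weaknesses follow from that choice.

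- **Information loss.** A participant just past the cut-off is treated like one far past it, and unlike one just short of it. With 50 participants there is little information to spare.
- **Misclassification.** If response is the overnight ambulatory change, each person's class depends on the difference of two single nights, so night-to-night variation enters twice. Nor is a fall from baseline in one person a treatment effect. The treatment group goes from horizontal to 6°, 12° and 18° without a 1° phase, so control information exists only between the groups, in weeks 2-3.

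At stake is a missed or blurred predictor in a study that is meant to inform the phase III population. The article describes no other predictor analysis.

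**Working it through.** The article gives no figure for this analysis, and no standard deviation (SD), effect size or alpha, so there is nothing of its own to reproduce. From the document come n = 50, one ambulatory recording per phase, and a change score taken against week 1. Everything else below is an assumption.

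**1. Information kept by a split.** For a normally distributed change cut so that a proportion p are responders, the correlation with a predictor shrinks by φ(z_p)/√(p(1−p)).
- Median split: 0.399/0.5 = 0.798. Squared, this is 2/π = 0.64, so about 64% of the information is kept.
- A cut giving 30% responders: 0.348/0.458 = 0.76, squared 0.58.

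The median is the most favourable single cut under normality, so another cut-off in an unseen analysis plan would not remove the loss.

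**2. Power at n = 50, two-sided 5%.** Simulation of the association between a predictor and the change:

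| Assumed true correlation | Change kept continuous | Median split |
|---|---|---|
| 0.3 | 57% | 39% |
| 0.4 | 83% | 63% |
| 0.5 | 97% | 84% |

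Repeat runs differ by one or two percentage points. Hand check for 0.3, by Fisher's z:
- Continuous: atanh(0.3) × √47 = 2.12, and Φ(2.12 − 1.96) = 0.56.
- Split: 0.3 × 0.798 = 0.239, atanh(0.239) × √47 = 1.67, and Φ(1.67 − 1.96) = 0.39.

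**3. Misclassification, if response is the overnight ambulatory change.** Let the true individual effect have SD τ and a single night have error SD e. The correlation between true and observed change is ρ = τ/√(τ² + 2e²). With the cut at the centre of the distribution, the share in the wrong class is 0.5 − arcsin(ρ)/π.

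| τ (mmHg) | e (mmHg) | ρ | Wrong class |
|---|---|---|---|
| 8 | 5 | 0.75 | 23% |
| 5 | 5 | 0.58 | 30% |
| 5 | 8 | 0.40 | 37% |
| 5 | 10 | 0.33 | 39% |
| 3 | 10 | 0.21 | 43% |

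A simulation of 400,000 persons (mean change and cut-off both −10 mmHg) gives the same range. If everyone had the same true effect, about half would still be labelled responders.

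**4. Is a false link with baseline severity created?** The same simulation was run with the effect independent of true baseline, a between-person SD of 15 mmHg and a clinic error SD of 10 mmHg. False-positive rates at n = 50:
- severity from the separate clinic test, errors independent: 4.4% to 5.5%, which is nominal;
- clinic and week-1 errors correlated at 0.3: 7% to 10%; at 0.5: 11% to 20%;
- severity from the week-1 ambulatory recording itself: 12% to 61%.

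**5. Power of the randomised contrast.** Testing severity by group (6° versus 1°, weeks 2-3, about 25 against 25) gives about 19%, 30% and 49% for correlations of 0.3, 0.4 and 0.5. That is less than the responder split.

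**The case against.** The strongest reply is that the article leaves the responder undefined. Response could be based on the daily supine morning BP, the guided standing tests or the orthostatic symptom questionnaire. Averaged morning readings would remove much of the single-night noise, and such a definition may properly sit in the full protocol or analysis plan. This stands. The absent definition is not a finding, and the misclassification range applies only if the ambulatory change is used. It does not rescue the split, because any definition that cuts a continuous change loses information.

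A reader might also infer that the plan builds in a false link, in which a chance-high baseline night makes a person look both severe and responsive. The text does not support that. It ties severity to the clinic tilt test, a separate occasion from the week-1 recording. With independent errors the false-positive rate is then about 5%. Large inflation needs severity to be taken from the week-1 recording, which is not proposed. Correlated errors would give moderate inflation, but the documents offer no figure for that correlation.

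Finally, the analysis is labelled exploratory, and the Discussion says that the study as a whole, not this comparison alone, will help determine the target population. Both points are correct and limit the weight. It is also not the case that the 1° phase goes unused, since the main model takes it as placebo.

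**Conclusion.** The point holds as a matter of method: the planned responder comparison is an inefficient way to look for predictors. At n = 50 a median split lowers power by about 18, 20 and 13 percentage points (57 to 39, 83 to 63, 97 to 84) for assumed correlations of 0.3, 0.4 and 0.5. Those figures assume normality and all 50 participants analysed; a per-protocol set would be smaller.

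Conditionally, if response is the overnight ambulatory change, roughly a quarter to two-fifths of participants would be misclassified, for effect SDs of 3-8 mmHg and single-night SDs of 5-10 mmHg. None of these SDs comes from the documents.

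A built-in false association with baseline severity is not established. The primary efficacy analysis is not affected. The change is worth making because it is cheap and the result may shape phase III.

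**What to change.** Replace the responder comparison by a continuous analysis in the planned mixed model, using all participants and phases:

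- Add baseline severity as continuous variables (supine BP and orthostatic fall from the tilt and standing tests) and their interactions with angle.
- State that severity comes from the first in-clinic visit, since the tilt test is repeated at the end.
- Report the estimates with confidence intervals, labelled exploratory. The power figures above compare a simple association with and without the split; they are not the power of these interaction terms.
- Report the randomised 6° versus 1° contrast in weeks 2-3 by severity as a supporting check on regression to the mean and time effects. Its power is too low for it to be the main test.
- If responder groups are still shown, keep them descriptive.

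The cost is revised wording, the added model terms and a slightly less simple presentation. No new data are needed and participants carry no extra burden.
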